## Abstract

**Background:**

Screening for gastrointestinal (GI) cancers, specifically colorectal cancer (CRC) and hepatocellular carcinoma (HCC), is often inadequately and inequitably implemented, leading to preventable morbidity and mortality. This protocol paper describes a study designed to compare the effectiveness of external facilitation with patient navigation across hospitals in the Veterans Health Administration (VA).

**Methods:**

Two hybrid type 3, cluster-randomized trials will compare the effectiveness of patient navigation versus external facilitation for supporting HCC and CRC screening completion. Twenty-four sites will be included in the HCC trial and 32 in the CRC trial, cluster-randomizing Veterans by their site of primary care. The primary outcome of reach of cancer screening completion will be measured after intervention and during sustainment. Multi-level implementation determinants (i.e., barriers and facilitators), preconditions, and moderators will be evaluated pre- and post-intervention, using Consolidated Framework for Implementation Research (CFIR)-mapped surveys and interviews of Veteran participants and provider participants.

**Discussion:**

Comparing findings in the two trials will allow researchers to understand how implementation barriers and strategies operate differently for a one-time screening in a relatively healthy population (CRC) vs. repeated screening in a more medically complex population (HCC).

**Trial registration:**

This project was registered at ClinicalTrials.Gov (NCT06458998) on 6/13/24.

**Supplementary Information:**

The online version contains supplementary material available at 10.1186/s13012-025-01448-1.

Contributions to the literature
This comparative effectiveness trial will compare two evidence-based implementation strategies to improve cancer screening reach.Comparing a patient-facing to a clinician-facing approach will offer novel insights into what works and for whom.This trial will assess mechanisms and heterogeneity of treatment effects to inform the science of implementation. 

## Background

Gastrointestinal (GI) cancers are among the most lethal and preventable cancers [1–4]. Specifically, colorectal cancer (CRC) and liver cancer (hepatocellular carcinoma, [HCC]), are the second and sixth leading causes of cancer death in the US [1, 3, 4]. Early cancer detection enables effective treatment, while delays lead to increased morbidity and mortality [5–8]. Because HCC most commonly occurs in people with cirrhosis, offering screening to this population is both effective and cost-effective [9, 10]. All major hepatology societies recommend HCC screening with imaging tests every six months for people with cirrhosis [11]. Similarly, because CRC death is preventable through rigorous screening programs, the US Preventive Services Task Force recommends CRC screening for all adults ages 45–75 [1]. CRC screening can start with colonoscopy or stool-based screening; abnormal stool tests must be followed with a timely colonoscopy [12, 13]. 

Despite clear evidence for HCC and CRC screening, more than 33 million people in the US who would be eligible have not had screenings [9, 11, 12, 14]. Nearly 80,000 deaths a year could be prevented if all people received the recommended GI cancer screenings [1–4]. It is therefore not surprising that CRC screening was designated as an important evidence-to-practice gap requiring implementation interventions in a recent Journal of the American Medical Association article [15]. Depending upon the provider, hospital system, and geographic area where people live, there is differential access to GI cancer screening [5–9, 16, 17]. These discrepancies suggest an urgent need to identify strategies to improve access to cancer screenings.

Implementation strategies are methods and techniques that are applied to support translation of evidence to practice in order to improve evidence-based care (e.g., cancer screening) [18, 19]. Such strategies range widely, from policy change to education, and can target patients, providers, and healthcare systems. However, no consensus exists regarding which implementation strategy is the most effective under what conditions and why [20–23]. Two of the most effective implementation strategies in health care are implementation facilitation (IF) and patient navigation. In IF, “facilitators” (implementation experts) deliver tailored provider-facing support, problem-solving tools, data, and education, in the context of a supportive relationship; IF has been rigorously tested [24–41]. Patient navigation (PN), or personalized patient support for care engagement, is supported by trials and systematic reviews, across the cancer care continuum and diverse patient populations [42–47]. However, it remains unclear how to select between these successful approaches to increase cancer screening. Therefore, this protocol outlines a study that will compare PN and IF, two evidence-based, widely used, and differently targeted strategies, addressing the question of who benefits most from patient-facing vs. provider-facing strategies to improve cancer screening. Likewise, defining the mechanisms of actions of complex strategies will aid in replication and scaling, a major implementation challenge [19].

## Methods/design

### Study aims and hypothesis

The reporting of this protocol is guided by the SPIRIT 2013 checklist [48]. The first aim of this study is to compare the effectiveness of PN and IF to increase the reach of HCC and CRC screening in the Veterans Health Administration (VA) using two hybrid type 3, cluster-randomized trials. The second aim will identify and compare how each implementation strategy addresses implementation barriers and improves patient engagement and patient-reported outcomes (PROs) using a convergent parallel mixed methods design. We hypothesize that PN will be associated with significantly increased HCC or CRC screening completion, compared to IF at 12 months post-intervention, based on literature about the effect sizes of these two approaches.

### Inclusion and exclusion criteria

VA sites are eligible if they are below the VA national median on GI cancer screening completion, where HCC screening is defined as abdominal imaging within the prior six months for Veterans with cirrhosis, and CRC screening is defined as receipt of colonoscopy within six months for Veterans with a positive stool test. We will include 24 sites in the HCC trial and 32 sites in the CRC trial. Veterans will be included and passively cluster randomized to their sites of primary care if they are 1) at least 18 years old, 2) eligible for CRC or HCC screening, and 3) enrolled in VA care in a recruited site with at least one encounter in the prior 18 months. For the HCC trial, we will define Veteran eligibility as having at least two ICD codes for cirrhosis or its complications in the electronic medical record. For the CRC trial, we will include Veterans over 45 years old who have had an abnormal fecal immunochemical test (FIT) or other screening stool test in the last 18 months. We will exclude Veterans who are not eligible for cancer screening due to receiving end of life care, defined as having a code for hospice, or who have a prior diagnosis of the cancer of interest. We will include healthcare providers or related staff working at participating VA sites who are engaged in CRC or HCC screening pathways.

### Recruitment

We will contact leadership at potential VA sites to participate in a 12-month intervention. Agreeable sites will be randomly assigned to the IF or PN arm; randomization will be stratified by site size (defined by median patients at risk of the cancer of interest) and structural characteristics (on-site vs. no on-site GI care). We will invite clinicians at participating sites to complete surveys and interviews at baseline and post-intervention to assess barriers, facilitators, preconditions, and moderators. At baseline and post intervention, a 10% subset of Veterans from the intervention sites will be mailed surveys. Post-intervention, a subset of patients will also be invited to complete follow-up interviews.

### Implementation strategies

#### Facilitation

Sites in the IF arm will participate in Getting To Implementation (GTI), a manualized intervention that guides users to select context-specific strategies with the help of a seven-step playbook, training, and external facilitation [49, 50]. GTI was adapted from Getting To Outcomes (GTO), RAND’s evidence-based program that has been successfully applied in VA and non-VA settings (e.g., Boys & Girls Clubs),[49–53] and tailored for GI cancer screening in VA using a mixed-methods, positive deviance approach (working with highly successful VA sites to identify effective strategies) [49, 50, 54, 55, 93–95]. Facilitators (one clinical expert and one evaluation expert per site) will guide site teams through the GTI steps during 1-h virtual meetings every other week for six months and provide as-needed maintenance calls for a total of 12 months of support (~ 20 h per site). Facilitators will follow best practices from VA’s Facilitation Manual to lead local providers and staff through goal setting, barrier identification, strategy selection, and iterative tests of change to improve processes of care, while engaging in interactive problem solving [24, 28, 49].

#### Patient navigation

PN sites will receive a Patient Navigation Toolkit during a one-hour introductory call with a team member who has expertise in patient navigation. The toolkit promotes three core activities with accompanying strong practices and resources: 1) using existing dashboards to identify Veterans, 2) conducting Veteran outreach to provide education, problem solve, and offer/schedule screening, and 3) documenting PN and clinical results [56]. After this introductory call, PN sites will be offered monthly opportunities to discuss progress with the experienced team member while submitting monthly tracking reports.

### Data collection

Patient data, including the primary outcome of receipt of guideline-concordant GI cancer screening, will be collected from the electronic medical records. These data will include demographic characteristics of eligible patients, rurality, area deprivation index, [57] comorbidities (organized into the Charlson score), [58] primary care provider, and relevant liver disease information (for the HCC cohort).

Site level data available from national sources include case load (number at risk and number served by VA), case mix (aggregated individual characteristics), facility complexity, region of the country, primary care panel size, and measures from the VA all-employee survey (e.g., psychological safety, servant leadership, empowerment). We will ascertain availability of resources (e.g., specialty care, on-site radiology or GI lab) from previously collected surveys. Data collection will also include pre- and post-intervention surveys and interviews with clinicians and staff from participating sites, using modified versions of the surveys shown in Table 1. We will conduct follow-up interviews with a subset of clinicians and patients.

**Table 1 Tab1:** Survey assessments

**Provider data**	
Implementation determinants	Consolidated Framework for Implementation Research (CFIR) survey
Patient-centeredness	Communication & Self-efficacy in Patient Centeredness [59]
Working Alliance	Working alliance
Implementation	Acceptability, appropriateness, feasibility [60]
Burnout	Maslach burnout inventory [61, 62]
**Veteran data**	
Health-related QOL	VR-12 [63]
Care experience	Survey of Healthcare Experience of Patients
Symptom experience	Symptoms surveys [64]
Interpersonal experience	Interpersonal processes of care
Shared decision-making	Satisfaction with decision-making (CollaboRATE) [65]
Patient activation	Modified Patient Activation Measure (PAM) [66]
Health literacy	Single item literacy screener [67]

### Outcomes

The study outcomes are illustrated in Table 2 and were mapped to the RE-AIM framework [68, 69]. Each trial is powered to assess differences in reach of GI cancer screening between the two arms at 12 months from baseline. The primary outcome for HCC screening is the receipt of HCC screening by ultrasound or contrasted imaging study. We will assess patients with a diagnosis of cirrhosis at each site, and evaluate whether they had HCC screening within the prior six months. The primary outcome for CRC screening is receipt of colonoscopy after an abnormal stool test for occult blood. For the CRC trial, we will assess whether patients with an abnormal stool-based CRC screening test completed a colonoscopy within six months. We will assess Effectiveness and Maintenance as patient-level outcomes, and Adoption and Implementation (including feasibility, acceptability, appropriateness) as site-level outcomes. Fidelity to and adaptations of the implementation strategies will be tracked monthly using standard data collection forms.

**Table 2 Tab2:** Outcome measures

Outcome	Specific Measure	Timepoints
**Reach** of CRC screening	CRC screening completion among patients with positive stool tests, representativeness of the population that receives screening (EMR)	Baseline & 12 months
**Reach** of HCC screening	HCC screening among Veterans with cirrhosis representativeness of the population that receives screening (EMR)	Baseline & 12 months
**Effectiveness** of screening	Tumor/polyp/lesion detection; linkage to cancer care (EMR) health benefits for rural and Black populations (EMR); change in quality of life (PRO)	Baseline & 12 months
**Adoption**	> 65% or 80% of eligible Veterans receive HCC or CRC screening, respectively (EMR)*,* reasons for non-adoption (Qu)	Baseline & 12 months
**Implementation**	How screenings and strategies are delivered	Ongoing
Feasibility	Feasibility of Intervention Measure [60] (Pr); meeting attendance, Qu	12 months
Acceptability	Acceptability of Intervention Measure [60] (Pr); Qu	12 months
Appropriateness	Intervention Appropriateness Measure (Pr); Qu	12 months
Fidelity	Whether strategies & screenings are delivered as intended (St)	Monthly
Adaptation	Changes to strategies over time (St, MADI, Qu)	12 months
Potential harm	Inequitable access (EMR), decreased engagement, trust, activation (EMR, Pt, Qu), provider mistrust, poor communication, burnout (Pr, Qu) [61, 62]	12 months
**Maintenance**	Follow-up of outcomes (EMR)	6 & 12 months post

Data Source: EMR = medical record, PRO = patient reported outcome, MADI = Model for Adaptation Design and Impact,  Pt = patient survey, Pr = provider survey, St = study team documentation, Qu = qualitative interviews

### Analysis

Results will be presented overall for each trial. We will use generalized linear mixed models (GLMMs) to assess the primary outcome of reach at 12 months. Time, intervention status, and the interaction will be modeled as fixed effects. Random effects will be included for clustering by site and Veteran. The parameters in the regression model and variance components will be estimated using the Maximum Likelihood or Restricted Maximum Likelihood. We will conduct a secondary analysis of the CRC outcome evaluating time to colonoscopy after abnormal stool test, using appropriate time-to-event models and conduct a sensitivity analysis that includes only Veterans with at least six months of follow-up after stool testing.

To understand whether and how the effectiveness of IF vs. PN varies between patients’ subgroups, we will conduct pre-specified exploratory secondary heterogeneity of treatment effect analyses. We will fit the same GLMMs as described above and include higher order interaction terms with subgroups of patients (e.g., rural vs. urban dwelling Veterans). The null hypothesis of homogenous treatment effect between Veterans within different subgroups for each outcome will be examined via interaction analysis (three-way interaction of time, treatment, and the subgroup of patients with decreased baseline rates [e.g., rural Veterans]; two-way interaction of treatment and subgroup of patients in the absence of a significant three-way interaction effect) using the same ANOVA type III Wald test based on either F- or Chi-square statistics as appropriate. In the presence of statistically significant treatment heterogeneity, we will fit a separate GLMM model for each subgroup of participants. For each outcome, the change scores from baseline to 12 months and their difference among the two treatments will be estimated using least square estimate with 95% confidence intervals for subgroups of patients.

We will assess the mechanisms of each strategy using Configurational Comparative Methods (CCM), which evaluate pathways and combinations of conditions that lead to improved PROs and cancer screening completion. Coincidence Analysis (CNA) is the CCM that we will use to incorporate both qualitative and quantitative data. Following data calibration and transformation, we will use the multi-value CNA function within the R “cna” package to identify combinations of conditions (solutions) that distinguish implementation and patient outcomes, based on the strongest parameters of fit (i.e., coverage and consistency). We will also compute a criterion of fit-robustness to avoid overfitting and to reduce model ambiguities. These findings will identify pathways through which PN and IF can address barriers to improve results.

We will evaluate the data from interviews and surveys independently, then conduct concurrent triangulation to evaluate areas where quantitative and qualitative data can be integrated, and examine convergence, expansion, discrepancy, and complementarity. We will use Rapid and rigorous qualitative data analysis coding, guided by the updated Consolidated Framework for Implementation Research (CFIR) [70]. Data will be double coded by two trained and experienced members of our team. Inter-coder reliability will be assessed using Cohen’s kappa statistic, with coding discrepancies resolved by joint critical review and revisiting until negotiated consensus is reached [71].

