### Sample size and power

Power calculations were informed by pilot data, literature, and similar studies. Estimates included VA data to calculate the mean number of eligible patients per site (811 ± 387 for HCC, and 429 ± 265 for CRC), coefficient of variance of cluster sizes (0.48 for HCC and 0.631 for CRC) within-person correlation of 0.2 (for HCC), and baseline screening rates. We applied a moderate ICC of 0.03 but varied the ICC up to 0.1 in our models. Based on literature demonstrating ~ 17% improvement in cancer screening with PN and ~ 9% improvement in screening with IF, we powered the study to detect an expected difference in screening rates between the PN vs. IF arms of 0.085 [24–47].

The cps.did.binary function in the R package clusterPower [72] was modified to include coefficients of variation of the cluster sizes using simulations (average of 1000 simulated data = 0.48 for HCC; 0.631 for CRC) and account for within-person and within-site correlation and validated these calculations using simulations that allow the hierarchical clustering [73]. Varying the parameters widely (e.g., difference in effect size as low as 0.03 between arms) and conducting over 1000 simulations, the HCC models demonstrated > 85% power with 12 sites per arm, and the CRC models retained > 80% power with 16 sites per arm.

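### The fixed effects listed for the primary model leave out the randomisation strata and let baseline means differ by arm: no bias, but precision is given up

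*Protocol article*

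**What the plan says.** Recruitment: "randomization will be stratified by site size (defined by median patients at risk of the cancer of interest) and structural characteristics", the structural characteristic being whether the site has GI care on site.

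Analysis: "We will use generalized linear mixed models (GLMMs) to assess the primary outcome of reach at 12 months". The terms are then given: "Time, intervention status, and the interaction will be modeled as fixed effects", and "Random effects will be included for clustering by site and Veteran". No stratification factor is named, and nothing sets the two arms to a common baseline mean. Table 2 collects reach at baseline and at 12 months.

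Inclusion and exclusion criteria: "We will include 24 sites in the HCC trial and 32 sites in the CRC trial". Sample size and power bases the calculation on a modified difference-in-differences routine for binary outcomes and reports that "the HCC models demonstrated > 85% power with 12 sites per arm, and the CRC models retained > 80% power with 16 sites per arm".

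**The concern.** Two features of the design are not used by the listed model.

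- **Strata.** Allocation was restricted by site size and on-site GI care. On-site GI care plausibly predicts how far colonoscopy completion can improve. If the strata predict change, an analysis that follows them removes that variation from the comparison of arms.
- **Baseline.** With time, arm and interaction all free, the interaction is a pure change-from-baseline contrast. It subtracts the whole chance baseline gap between arms, although randomisation makes the expected gap zero. A model with a common baseline mean subtracts only the part that predicts the 12-month value. It also makes the time-by-arm contrast coincide with the 12-month arm difference that the article names as its primary question.

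With 12 and 16 sites per arm, precision comes mainly from the number of sites, so such gains cannot easily be had in another way.

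**Working it through.** **Inputs from the article (Sample size and power).** Mean eligible patients per site with SD, "811 ± 387 for HCC, and 429 ± 265 for CRC"; coefficients of variation of cluster size, "0.48 for HCC and 0.631 for CRC"; ICC 0.03, varied up to 0.1; within-person correlation 0.2 for HCC; target difference 0.085; K = 12 and 16 sites per arm.

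**Assumptions, not in the article.** Baseline rate p = 0.5; within-person correlation 0 for CRC; two-sided 5% test; correlation of a site's effect between the two periods (CAC) of 1, 0.8 or 0.5.

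**Formulas.**
- Sampling part of a site mean: e = p(1−p)(1−ICC)(1+CV²)/m. Variance of a site mean: V = p(1−p)·ICC + e.
- Correlation of a site's baseline and 12-month means: r = (CAC·ICC·p(1−p) + ρ·e)/V, where ρ is the within-person correlation.
- Free baseline: variance = (2/K)·2(1−r)V. Common baseline: (2/K)·(1−r²)V. Ratio = (1+r)/2. The factor p(1−p) cancels, so the ratio does not depend on the assumed rate.

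**The plan's own power figures.** These cannot be tied to one set of inputs, because alpha, baseline rate and CAC are not given and the figures are lower bounds over varied settings. At a difference of 0.085, ICC 0.03 and CAC 1, power with a free baseline is about 100% in both trials, which is consistent with the stated bounds. At 0.03, the lowest difference the article mentions, the same formula gives 82.5% (t) or 85.7% (normal) for HCC and 54% or 57% for CRC. The CRC shortfall is a separate matter.

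**Common baseline, ICC 0.03.**
- HCC: e = 0.25 × 0.97 × 1.2304/811 = 0.000368; V = 0.0075 + 0.000368 = 0.007868. At CAC 1, r = (0.0075 + 0.2 × 0.000368)/0.007868 = 0.963.
- CRC: e = 0.25 × 0.97 × 1.3982/429 = 0.000790; V = 0.008290. At CAC 1, r = 0.0075/0.008290 = 0.905.

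| Trial | CAC | r | Variance saved | SE, free to common | Power at 0.085, free to common |
|---|---|---|---|---|---|
| HCC | 1 | 0.963 | 1.9% | 0.0099 to 0.0098 | about 100% both |
| HCC | 0.8 | 0.772 | 11% | 0.0245 to 0.0230 | 91.3% to 94.1% |
| HCC | 0.5 | 0.486 | 26% | 0.0367 to 0.0316 | 60% to 73% |
| CRC | 1 | 0.905 | 4.8% | 0.0141 to 0.0137 | about 100% both |
| CRC | 0.8 | 0.724 | 14% | 0.0239 to 0.0222 | 93.0% to 95.9% |
| CRC | 0.5 | 0.452 | 27% | 0.0337 to 0.0287 | 69% to 82% |

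Power uses the noncentral t with 2K−2 degrees of freedom (free) or 2K−3 (common). At ICC 0.1 the variance saved is 0.5%, 10% and 25% (HCC) and 1.4%, 11% and 26% (CRC) for CAC 1, 0.8 and 0.5.

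**Chance baseline gap between arms.** SD = √(2V/K) = √(2 × 0.007868/12) = 0.036 (HCC) and √(2 × 0.008290/16) = 0.032 (CRC), or 3.6 and 3.2 points against a target of 8.5.

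**Strata, main effects alone.** A stratum effect that is constant over time cancels from the time-by-arm contrast. A simulated logistic mixed model (site intercept, one two-level stratum explaining 30% of between-site variance, no Veteran effect) gave the same interaction SE with and without it: 0.0421 and 0.0421 (HCC), 0.0505 and 0.0505 (CRC), on the logit scale.

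**Strata by time.** If the error term is between-site variation in change, and the strata explain a share R of it, the HCC interval-width ratio is √(1−R) × t(0.975; 19)/t(0.975; 22) = √(1−R) × 2.093/2.074, allowing 3 degrees of freedom for the strata. This is 1.009 at R = 0, 0.984 at 5%, 0.957 at 10% and 0.903 at 20%. The article gives no value for R.

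**The case against.** The strongest reply is that the listed model is a coherent, standard choice. Time, arm and interaction is a difference-in-differences analysis, the power simulation is of the same type, and planned power therefore does not rest on the precision in question. That stands.

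It can also be said that the list is not declared exhaustive. The article is condensed, its limitations section speaks of covariates in connection with the primary analysis, and case load and on-site resources are among the data to be collected. The full protocol or SAP may add the strata. This limits the point to the terms as listed: a reader might infer that the model contains nothing else, and the article does not say so. But the mention of covariates does not place either stratum in the model, and the fixed effects are stated positively.

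Two stronger readings should be resisted.
- **A conservative test.** One might infer that ignoring the strata makes the listed model test at about 3% instead of 5%, since 2·P(T₂₂ > 2.074/√0.8) = 0.030. That needs R = 20% and an error term built on between-site variation in change. The article names random effects for site and Veteran and no site-by-time term. With CAC 0.8, the simulated site-intercept model gave a mean SE of 0.042 against an empirical 0.107 (HCC, logit scale), so the error would run the other way. That is a separate and larger question.
- **Bias from regression to the mean.** Sites are chosen for below-median performance, but the selection precedes randomisation and applies to both arms, so it is equal in expectation.

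**Conclusion.** The point holds as one of efficiency and of alignment with the design. The listed fixed effects omit both stratification factors and leave baseline means free by arm. The estimate is not biased by this, and the stated power is not undermined by it.

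The size is uncertain. The gain from a common baseline is slight (about 2% of variance in HCC, 5% in CRC) under the stable site effects that a site intercept alone implies. It becomes material, 11% to 27%, only if site effects shift over the year (CAC 0.8 to 0.5). The gain from the strata runs from a loss of about 1% in HCC interval width to a saving of about 10%, and it arises only with stratum-by-time terms and an error term that reflects variation in change. The mismatch between allocation and listed model can be read directly from the text. The magnitudes rest on CAC and R, which the article does not give.

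**What to change.** In both primary models, add site-size stratum and on-site GI care **and their interactions with time** as fixed effects; main effects alone do not change the time-by-arm contrast. Constrain the arms to a common baseline mean by dropping the free intervention effect at baseline, or use a site-level ANCOVA on the baseline rate. Keep the model as now listed as a sensitivity analysis. If the SAP already does this, a sentence in the article's Analysis section is enough.

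The larger gains at CAC below 1 need a model that lets site effects differ between periods, or the site-level ANCOVA, which estimates the weight on baseline from the data.

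The cost is wording and about 2 to 3 between-site degrees of freedom for the strata; the ANCOVA slope takes one more. No new data are needed. The choice should be fixed before outcome data are seen, so that covariates are not chosen after the fact.

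### As written, the primary GLMM leaves out site-by-time variation, so the time-by-arm test can reject too often if sites change differently over the year

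*Protocol article*

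**What the plan says.** The Analysis section specifies the primary model for reach at 12 months. On the fixed part it says "Time, intervention status, and the interaction will be modeled as fixed effects". On the random part it says "Random effects will be included for clustering by site and Veteran". On estimation, the regression parameters and "variance components will be estimated using the Maximum Likelihood or Restricted Maximum Likelihood". It names no site-by-time effect, random time slope by site, robust variance or site-level analysis.

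Table 2 (Outcomes) lists reach in both trials at "Baseline & 12 months", so each site contributes two periods.

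The Sample size and power section modifies a difference-in-differences power function for binary outcomes to carry within-person and within-site correlation. On the latter it says "We applied a moderate ICC of 0.03 but varied the ICC up to 0.1 in our models". It gives no correlation between a site's baseline and 12-month levels. With parameters varied widely, including a between-arm difference as low as 0.03, it reports that "the HCC models demonstrated > 85% power with 12 sites per arm" and "the CRC models retained > 80% power with 16 sites per arm".

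**The concern.** Sites are randomised, so the evidence on navigation versus facilitation comes from 24 or 32 independent units. In a two-period model with a site intercept, the time-by-arm interaction compares changes within sites, and the intercept drops out of each change. A Veteran intercept drops out in the same way. What remains in the model's standard error is patient-level binomial noise, which becomes very small with hundreds of patients per site.

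The model then has nowhere to put the ordinary fact that some sites improve and others slip over a year. The article itself gives reasons to expect this. Facilitation sites choose strategies to suit local conditions (Facilitation), and the Discussion asks for which kind of site each strategy works better. If such variation exists, a nominally significant difference between arms could be site drift, and the confidence interval would be too narrow. The same GLMM is reused for the subgroup analyses.

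**Working it through.** **Inputs from Sample size and power.** Sites per arm k = 12 (HCC) and 16 (CRC). Mean patients per site m = 811 and 429, so patients per arm and period are 12 × 811 = 9,732 and 16 × 429 = 6,864. Coefficients of variation of site size are 0.48 and 0.631. ICC is 0.03, varied up to 0.1. Within-person correlation r is 0.2 for HCC. Differences are 0.085 (design) and 0.03 (lowest mentioned).

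**Assumptions.** Two-sided 5% test. Baseline rate p = 0.5, because no figure is given (0.2 to 0.8 tried for power). CAC is the correlation between a site's effects at baseline and 12 months, and it is not given. For HCC, r runs from 0 (different Veterans in each period) to 0.2. For CRC, r = 0.

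**Formula.** For the difference in changes between arms, on the proportion scale:

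SE² = (4/k) · p(1−p) · [(1−ICC)(1−r)/m + ICC(1−CAC)]

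A model with constant site and Veteran effects has CAC = 1, and the second term vanishes.

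**Step 1: the plan's own power.** Power = Φ(difference/SE − 1.96), with CAC = 1 and ICC 0.03.

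- HCC, r = 0.2: SE² = 0.0833 × (0.97 × 0.8/811), SE = 0.0089, power at 0.03 = 0.92. With r = 0, SE = 0.0100 and power = 0.85. This fits the stated figure.
- CRC: SE² = 0.0625 × (0.97/429), SE = 0.0119, power at 0.03 = 0.71 at p = 0.5, 0.79 at p = 0.3 or 0.7, and 0.88 at p = 0.2 or 0.8. The stated figure is reached at 0.03 only for rates well away from 50%. At 0.085 power is 1.00.
- Alternative reading, arms compared at 12 months only: design effect 1 + [(1+CV²)m − 1] × ICC = 30.9 (HCC) and 19.0 (CRC). Power is 0.57 and 0.63 at 0.085, and 0.11 and 0.12 at 0.03. This does not fit the stated power.

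**Step 2: let sites change differently.** At CAC 0.8 the second term is 0.03 × 0.2 = 0.006. The HCC SE (r = 0.2) rises from 0.0089 to 0.0241, and the CRC SE from 0.0119 to 0.0227.

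**Step 3: type I error of the model as written.** Error = 2[1 − Φ(1.96 × SE at CAC 1 / true SE)]. The ratio does not involve p. The site-to-site SD of change is √[2p(1−p) · ICC · (1−CAC)].

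| CAC (ICC 0.03) | SD of site change | HCC SE ratio | HCC error, formula | HCC, simulated | CRC SE ratio | CRC error, formula | CRC, simulated |
|---|---|---|---|---|---|---|---|
| 1 | 0 | 1.0 | 5% | 6% | 1.0 | 5% | 5% |
| 0.99 | 1.2 points | 1.1 | 8–9% | 8% | 1.06 | 7% | 5% |
| 0.95 | 2.7 points | 1.5–1.6 | 19–22% | 23% | 1.29 | 13% | 14% |
| 0.9 | 3.9 points | 1.9–2.0 | 30–34% | 27% | 1.53 | 20% | 20% |
| 0.8 | 5.5 points | 2.5–2.7 | 42–47% | 46% | 1.91 | 31% | 37% |

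The simulated columns come from logistic random-site-intercept GLMMs fitted to binary data with no true difference and with site sizes varying at the stated coefficients (400 runs per cell; Monte Carlo SE about 1 point near 5% and 2.5 points near 40%). They use different Veterans in each period and no Veteran effect. On the same data, a t-test on site-level changes rejected in 3–7% of runs.

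At CAC 0.9 the formula gives 15–17% (HCC) and 10% (CRC) for ICC 0.01, and 54–58% and 41% for ICC 0.1.

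**Step 4: power once site-by-time variance is counted.** t-test on 2k − 2 = 22 or 30 degrees of freedom, p = 0.5, HCC r = 0.2.

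| ICC | CAC | HCC at 0.03 | CRC at 0.03 | HCC at 0.085 | CRC at 0.085 |
|---|---|---|---|---|---|
| 0.03 | 0.95 | 0.52 | 0.47 | 1.00 | 1.00 |
| 0.03 | 0.9 | 0.35 | 0.36 | 0.99 | 0.99 |
| 0.03 | 0.8 | 0.22 | 0.25 | 0.92 | 0.95 |
| 0.03 | 0.5 | 0.12 | 0.14 | 0.61 | 0.71 |
| 0.1 | 0.8 | 0.10 | 0.12 | 0.50 | 0.60 |

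**The case against.** **The sentence on random effects does not say intercepts only.** A site-level time effect could be meant, and an unseen SAP may contain one. That possibility stands. But the article states its random-effects structure, and its power section carries the same two components and no third. As written, it describes the model tested above.

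**The article does not say that the primary contrast is the interaction.** It speaks of reach at 12 months and of differences between arms at that time. If the 12-month arm difference were tested, site variance would stay in the standard error, and the ratio of true to model SE would be only about √[2/(1+CAC)], or 1.03 at CAC 0.9 and 1.05 at 0.8. The ambiguity is real and should be removed. But that reading gives about 57% (HCC) and 63% (CRC) power at the design difference, well short of the stated figures, whereas a difference-in-differences reading fits.

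**The size depends wholly on a quantity the article does not give.** This stands. At CAC 1 the test is sound, and at 0.99 with ICC 0.03 the excess is small. A reader might infer that the error rate is certainly far above 5%; the documents do not support that without a CAC.

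**Other inferences that go too far.**

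- That the stated power proves zero site-by-time variance. It is only consistent with it: CRC power at 0.03 is about 71% at a 50% rate even with CAC 1, and the article does not say that 0.03 and an ICC of 0.1 were combined.
- That the CRC Veteran effect cannot be estimated. The 18-month stool-test window could place a Veteran in both periods.
- That the primary test is a chi-square Wald test. That wording belongs to the subgroup analyses and also allows F.

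**Conclusion.** The concern holds in conditional form. Followed as written, and with the interaction as the treatment effect, the primary test in both trials treats site-specific change as zero although sites are the randomised units. A site-to-site SD of change of 2.7 percentage points (CAC 0.95, ICC 0.03, 50% rate) is enough to raise the type I error to about 13–14% in CRC and 19–23% in HCC. The error ranges assume an ICC of 0.03, and larger ICCs make them worse.

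The power claim at differences as low as 0.03 relies on essentially no site-by-time variance; at CAC 0.95 it is about 50% in both trials. The design difference of 0.085 is much safer: at ICC 0.03, power stays above 90% for CAC of 0.8 or more. The trials therefore remain viable over that range, and the matter should be settled before the primary analysis.

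**What to change.** - State that the primary contrast is the time-by-arm interaction.
- Add a site-by-time random effect to the primary GLMM in both trials, and carry it into the subgroup models that reuse it.
- Test the interaction with a small-sample correction on site-level degrees of freedom, about 22 for HCC and 30 for CRC. Name a site-level analysis of the change in proportions as the fallback if the model does not converge.
- Restate power over a stated range of CAC and ICC, with the baseline rates used.
- If the full SAP already contains the term, say so in the article.

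The cost is wording, one more variance component and a rerun of the power simulations. Confidence intervals will be wider, and stated power for small differences will be lower.
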